**Fig. 2 Fig2:**
[figure not shown]
Illustration of the target line and the “live” applied muscle force participants will be seeing during an isometric handgrip (IHG) training session

Participants will be instructed to breathe at a normal rhythm and depth during IHG training in order to avoid Valsalva maneuvers. To ensure that participants work at 30% MVC throughout the trial, the 30% MVC will be adjusted in the intervention period (after 5, 10, and 15 weeks) according to a previously described method [10].

The usual-care group will have the same number of hospital visits for measurements of blood pressure and MVC as the intervention group in order to ensure similar attention provided by the healthcare professionals.

### Assessment protocol

Prior to the randomization process, participants will undergo demographic and physiological baseline assessments by an experienced assessor. Demographic measures will include: gender, age, height, Body Mass Index (BMI), level of physical activity using the International Physical Activity Questionnaire (IPAQ) [15], co-morbidities, alcohol intake, smoking status, and number and type of medical drugs. Participants will be given advice on lifestyle changes according to the national guidelines including, but not limited to, the DASH Diet [16], reduced alcohol intake, cessation or reduction of smoking, and advice on an active lifestyle [13]. Following randomization all participants will return to Aalborg University Hospital at weeks 5, 10, 15, and 20 for follow-up assessments (see Fig. 3 for an overview based on the SPIRIT Figure) in a controlled environment. At the follow-up measures, participants will be specifically asked not to mention nor comment on which group they have been assigned to in order to maintain allocation concealment to the outcome assessor. With respect to physiological measures, these will be assessed approximately at the same time of day as the baseline measures to avoid variability due to circadian rhythms or medication intake cycle. In addition, participants will be instructed via telephone by the study coordinator to refrain from vigorous exercise and alcohol for 24 h prior to all measurements. Moreover, they will be instructed to fast and refrain from caffeine for 4 h prior to all measurements. Further, they will be instructed to refrain from smoking and intake of anti-hypertensive medicine up to 30 min prior to all measurements. In addition, the assessor will ask if the participants complied with these instructions. The noise level and room temperature (20–23 °C) will be controlled by the assessor prior to the assessments. Finally, participants will be asked to empty their bladder, if possible, before tests by the assessor.

**Fig. 3 Fig3:**
[figure not shown]
Schedule of enrollment, interventions, and assessments

### Outcome measures

#### Primary outcome measure

The primary endpoint in the study is SBP, which will be measured using a standard hospital electrical sphygmomanometer (Omron Comfort M6 AC). After the participants have been relaxing for 5–10 min the SBP measurements are performed on the left arm while it is resting on a table. Participants will be instructed to sit with their legs parallel and to stay quiet during the measurements. SBP will be measured three times in the left arm with rest periods of 1 min between measurements. The average of the three measures at baseline will be used for analysis. For the home SBP recordings the participant will be asked to follow the same procedures (and use the same device) as described above and perform recordings on the same weekday and timeframe as their baseline tests at the hospital. The home measures will be performed prior to commencement of the IHG training on the relevant day.

#### Secondary outcome measures

Diastolic blood pressure (DBP) and heart rate (HR) will be measured using the same procedure as described above for SBP. Exerted force (maximum voluntary force, rate of force development, and force variability) will be measured in both hands using the same procedure as described in detail previously [10, 17, 18]. Further, at the end of each training session participants are asked to self-report pain intensity using a Visual Analog Scale (VAS) [19] for each hand. The VAS reports values between 0 and 10 with 0 corresponding to no pain and 10 to maximum pain. Finally, compliance of the IHG training group will be monitored by a computer-generated report every week during the intervention period.

### Data analysis

Study data will be collected and managed using REDCap electronic data capture tools hosted at Aalborg University Hospital [20]. REDCap (Research Electronic Data Capture) is a secure web-based application designed to support data capture for research studies, providing (1) an intuitive interface for validated data entry; (2) audit trails for tracking data manipulation and export procedures; (3) automated export procedures for seamless data downloads to common statistical packages; and (4) procedures for importing data from external sources. In addition, the study has been reported to the Danish Data Protection authorities.

Statistical analysis of data will be performed using SPSS (Version 22, IBM Corporation, Armonk, NY, USA). Prior to all statistical analysis the dataset will be explored according to parametric test assumptions, and, if violated, an appropriate transformation or statistical method will be applied. Further, statistical analysis will be conducted according to the intention-to-treat principal. However, a sensitivity analysis using the per-protocol principal will also be performed. This will only include participants who have completed minimum 50% of their training sessions (480 min). The between-group difference in the ∆ change from baseline to the 20-week follow-up mark for the primary endpoint will be analyzed using a linear mixed-effects model. Secondary outcomes will also be analyzed using a linear mixed-effects model. Besides these primary analyses a number of sub-analysis will also be performed. Exploring difference in effect of training whether on blood pressure regulating medicine or not, age, gender, and physical activity level (IPAQ). Finally, an analysis of variance (ANOVA) model will be applied after 10 weeks of training to explore if there exists a leveling-off effect on SBP in the IHG group.

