Recently, we have shown that handgrip [10] and lower extremity strength [11] can be measured precisely using a standard Nintendo Wii Board (Wii) with an on-screen visual feedback of the force exerted over time (force/velocity curve). As a continuation of this work, we have further developed a novel method that monitors handgrip muscle control and is suitable for IHG home training. Given the development and low-cost nature of the Wii, we are now able to perform home-based IHG training. For the above reasons we intend to conduct a IHG training study, which will be twice as long (20 weeks) as the longest previous study (10 weeks) to explore the effects on specific measures of blood pressure and other relevant outcomes. Our primary aim is to explore the effects of 20 weeks’ IHG home training facilitated by a Wii in hypertensive older adults (50 + years of age) in lowering SBP. Secondary aims are to explore if/when a leveling-off effect on SBP will occur during the 20-week intervention period in the training group and to explore adherence and potential harms related to the IHG home training. The study will compare IHG home training with a control group in a randomized, assessor-blinded design. Thus, we hypothesize (1) that 20 weeks of IHG home training will significantly reduce SBP in hypertensive older men and women compared to usual care, (2) that a leveling-off effect on SBP will occur during the 20 weeks of IHG training, and (3) that a minimum of 50% of participants will complete at least 50% of their training sessions (30 sessions).

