## Methods/design

### Design

The design of the study will be a randomized controlled, outcome-assessor-blinded superiority trial with participants randomly assigned to either an intervention group (IHG home training + hypertension guidelines on lifestyle changes) or to a control group (hypertension guidelines on lifestyle changes). The length of the study will be 20 weeks and the IHG training will be performed in the participant’s own home. Randomization will be made using a computer-generated block randomization with 1:1 allocation between the intervention group and the usual-care group (see Fig. 1). The protocol follows the Standard Protocol Items: Recommendations for Interventional Trials (SPIRIT) 2013 guidelines Additional file 1 [12].

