### IHG training group and usual-care group

Participants of the intervention group will follow the home-based IHG training protocol for 20 weeks. The IHG training consists of isometric contractions applied with the hands on a Wii. The Wii will be connected to a standard PC to monitor the level of the applied force using the FysioMeter software (Brønderslev, Denmark). The IHG training will be structured with four sets of 2-min contractions for each hand, 3 days per week for 20 weeks. The training volumes will this way sum up to a total of 480 min for each hand in the study period. The level of IHG training will be set to 30% MVC in line with previous IHG training trials [7, 9]. During training sessions, participants will be seated on a standard chair with the non-working hand holding on to the Wii at the middle of the board, while the working hand will grab the corner of the Wii (see Fig. 2). Participants will alternate between the left and right hand with a 1-min resting period between changing hands. The software displays the target force level (30% MVC) on-screen as a horizontal line (yellow line, see Fig. 2) and participants will apply the required force level on the Wii according to this line (black line, see Fig. 2). Participants will be asked to do the IHG training every other weekday (i.e., Monday, Wednesday, and Friday) allowing for restitution between training days.

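### The per-protocol rule can be applied only to the IHG arm, so that sensitivity analysis is not a randomisation-protected check on the intention-to-treat result

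*Protocol article*

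**What the plan says.** The Data analysis section makes intention-to-treat the governing principle and adds a per-protocol analysis as a sensitivity analysis. Its population is defined in one sentence: "This will only include participants who have completed minimum 50% of their training sessions (480 min". No separate rule is given for usual-care participants.

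The training schedule, under IHG training group and usual-care group, is "four sets of 2-min contractions for each hand, 3 days per week for 20 weeks", which the article says will "sum up to a total of 480 min for each hand in the study period". The Background states the same 50% level in sessions, as the third hypothesis: "a minimum of 50% of participants will complete at least 50% of their training sessions (30 sessions".

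The comparator, under Design, is lifestyle advice only: "or to a control group (hypertension guidelines on lifestyle changes". Its contact is matched through measurement visits: "The usual-care group will have the same number of hospital visits for measurements of blood pressure and MVC as the intervention group". The weekly computer-generated compliance report, under Secondary outcome measures, covers the IHG group alone.

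**The concern.** The population for a between-group comparison is defined by a criterion that only one of the two groups can meet. Usual-care participants have no sessions, so the sentence either excludes them all or is silently not applied to them. In the second case one randomised arm is filtered by behaviour after randomisation and the other is not.

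The matter at stake is how the sensitivity analysis will be read. Both arms receive advice on diet, alcohol, smoking and activity. People who keep up a home programme for 20 weeks may also be those who act on that advice, and then adherers could show a larger fall in SBP than all controls even if the training did nothing. Agreement between the per-protocol and intention-to-treat results would look like confirmation without being one.

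A smaller point of labelling goes with it. The article uses 480 min for the full planned volume of each hand and again, with no stated basis, for the 50% threshold.

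**Working it through.** **1. Reproducing the 480 min.** The inputs are four 2-min contractions per hand, 3 days a week, for 20 weeks (IHG training group and usual-care group).

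- Sessions: 3 × 20 = 60. Half is 30, which agrees with the Background.
- Minutes per hand per session: 4 × 2 = 8.
- Full plan: 60 × 8 = 480 min per hand; × 2 = 960 min over both hands.
- Half the plan: 30 × 8 = 240 min per hand; × 2 = 480 min over both hands.

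So 480 min is 100% of the per-hand volume and exactly 50% of the two-hand volume. The threshold figure reproduces once the hands are summed.

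**2. Who can meet the rule.**

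| | IHG arm | Usual-care arm |
|---|---|---|
| Training sessions planned | 60 | none |
| Compliance report | weekly | none |
| Can complete at least 50% of sessions | yes or no, by participant | not defined |

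The rule sorts IHG participants and says nothing usable about controls.

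**3. How much selection is possible.** The adherence hypothesis would be met if half of the participants reached the threshold. The plan therefore contemplates that up to about half of the IHG arm might be left out.

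**4. Illustrative size.** Suppose training has no effect, all controls are kept, and only the fraction p of the IHG arm with the highest adherence is retained. Let adherence and SBP reduction be jointly normal with correlation r. The spurious difference is

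b = r × SD × φ(c)/p, with c = Φ⁻¹(1 − p).

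SD = 8 mmHg is the value assumed for the IHG arm under Sample size. The values of r and p are my assumptions; the article gives no data on either. The factor φ(c)/p is 0.798 at p = 0.5. For example, 0.5 × 8 × 0.798 = 3.19 mmHg.

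| p retained | r = 0.1 | r = 0.2 | r = 0.3 | r = 0.5 |
|---|---|---|---|---|
| 50% | 0.64 | 1.28 | 1.91 | 3.19 |
| 70% | 0.40 | 0.79 | 1.19 | 1.99 |
| 90% | 0.16 | 0.31 | 0.47 | 0.78 |

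The range is 0.16 to 3.19 mmHg, or 0.16/7 = 2% to 3.19/7 = 46% of the planned 7 mmHg. For scale, the standard error of the planned comparison with 20 per arm and SDs of 8 and 9 is √(64/20 + 81/20) = √7.25 = 2.7 mmHg. A negative r gives the same sizes with the opposite sign.

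**The case against.** The strongest reply has four parts.

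*The threshold is clear.* This stands. A reader might infer that 480 min is an error, or that the cut-off could mean 60 sessions rather than 30. The article does not support that. The same sentence says 50%, the Background says 30 sessions, and the two-hand arithmetic gives 480 exactly. Only the missing label remains.

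*Nobody would really drop the controls.* This largely stands as a forecast of practice. The planned analysis is a between-group difference, so controls must be present. But it leads straight to the other reading, adherers against all controls, which is where the selection arises. Nor is this a detail merely left to a fuller document: the article states the inclusion rule, in a form that works for one arm.

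*Every per-protocol analysis loses the protection of randomisation, and this one is secondary.* The second half stands and limits the weight of the point. The first half is true in general, but here the filter falls entirely on one arm.

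*The bias is assumed, and the remedy adds little.* Both parts stand. A reader might infer that the analysis is biased in favour of IHG. The article contains no data linking adherence to SBP change or to uptake of lifestyle advice, so neither size nor direction can be asserted, and at the low end the bias is negligible. It is also true that, with no training in the control arm, a simple complier-average estimate is the intention-to-treat effect divided by the proportion complying. It does not test the result independently.

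**Conclusion.** The per-protocol sensitivity analysis rests on an inclusion rule that only the IHG arm can satisfy. As it would most likely be run, it compares selected adherers with unselected controls. It is at risk of selection bias and cannot serve as a randomisation-protected check on the primary result.

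The risk is about 0.2 to 3.2 mmHg in absolute size against the planned 7 mmHg. That holds under no true effect, joint normality, SD 8 mmHg, all controls kept, correlations of 0.1 to 0.5 and 50% to 90% of the IHG arm retained. Only the SD and the 7 mmHg come from the article.

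A reader might go further and doubt the primary conclusion. That does not follow: the main analysis is by intention to treat and is untouched. The point is worth correcting, but it concerns a supporting analysis only.

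**What to change.** - Keep intention-to-treat as the primary analysis.
- Write the threshold as at least 30 of 60 sessions (240 min per hand, 480 min over both hands).
- For the effect of adherence, use a complier-average analysis, or a dose analysis with sessions completed as the exposure. Either should use random assignment as instrument and include all randomised participants in both arms. The weekly compliance report already supplies the exposure.
- If the adherers-versus-controls comparison is kept, state that all usual-care participants enter and label it descriptive.

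The change is one of analysis wording and needs no new data. The price is a wider confidence interval and an added assumption. The binary version assumes no effect below the threshold, so 29 sessions would count as none. The dose version assumes a dose-response shape. The binary estimate essentially rescales the intention-to-treat effect: if half comply, the estimate and its standard error both roughly double (1/0.5 = 2). It should therefore be reported as an estimate of the effect among compliers, not as independent confirmation.

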### Sample size

Based on previous evidence [14], and using a more conservative approach, we carried out an a priori power analysis assuming a 7-mmHg difference in the ∆SBP between the IHG training and the usual-care group (favoring the IHG training group) after 20 weeks of training. In addition, we assumed the standard deviation of the IHG training and usual-care group to be 8 and 9 mmHg, respectively. We further choose a power of 80% and an alpha level of 5% with equal group sizes. This resulted in a total sample size of 40 participants with 20 in each group. Assuming a 25% loss to follow-up, we would need to recruit 25 participants in each group.

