### Recruitment and randomization procedure

Participants will be recruited consecutively by their local physician, through bulletin, newspaper advertisement, local senior citizens’ centers, and health/activity clubs. Eligible subjects, who agree to participate, will be asked to provide an informed written consent, undergo baseline assessment, and will thereafter be randomized to one of the two arms: (1) IHG training or (2) usual care. Participants will randomly be assigned by computer-generated random numbers in permuted blocks to attend either arm for 20 weeks. The randomization will be stratified according to gender (male/female). A third party not involved in the day-to-day running of the study will perform group allocation and will notify the study coordinator by e-mail to ensure concealed allocation.

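### The primary change-from-baseline comparison names neither baseline SBP nor the stratification factor as a model term; stating both would gain precision at almost no cost

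*Protocol article*

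**What the plan says.** The Data analysis section defines the primary contrast as the between-group difference in "change from baseline to the 20-week follow-up mark for the primary endpoint will be analyzed using a linear mixed-effects model". It gives the contrast and the class of model and lists no model terms.

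The Sample size section uses the same quantity: "we carried out an a priori power analysis assuming a 7-mmHg difference in the" change in SBP between the arms after 20 weeks. It adds that "we assumed the standard deviation of the IHG training and usual-care group to be 8 and 9 mmHg, respectively". Covariate adjustment is not mentioned there either.

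Allocation uses permuted blocks within gender: "The randomization will be stratified according to gender (male/female". In the analysis text gender appears only in a list of sub-analyses of differential training effect, alongside blood-pressure medication, age and physical activity level.

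Baseline SBP will be known for every participant before allocation. The Assessment protocol places the baseline assessment ahead of randomisation, and the primary outcome section takes the mean of three readings.

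**The concern.** A change score without a baseline term is an analysis of week-20 SBP in which the slope on baseline is fixed at 1. When the true slope is below 1, as regression to the mean implies, this over-subtracts the baseline. The arm that happens to start higher then tends to show the larger fall whatever the treatment does. Averaged over randomisations this cancels. In the one trial that is run it is extra error, and baseline adjustment removes it.

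The stratum raises a smaller issue. Stratified allocation balances the arms on gender. If gender predicts the outcome and is left out of the model, the standard error does not reflect that balance and tends to be slightly too large.

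The trial plans for only 20 evaluable participants per arm, so it has little precision to give away.

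**Working it through.** **Inputs from the Sample size section.** Difference 7 mmHg; SDs 8 and 9 mmHg; power 80%; alpha 5%, sidedness not stated; 20 evaluable and 25 recruited per arm; 25% loss.

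**Assumptions not in the protocol.** The SDs are SDs of change (their scale is not stated; the effect is on change). SBP has equal variance at baseline and week 20. The baseline to week-20 correlation r lies between 0.4 and 0.8.

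**Step 1: the plan's own figure.** Pooled SD = √((8² + 9²)/2) = √72.5 = 8.51. By the normal approximation, n per arm = 2(z_α + z_β)² × 72.5/7².
- Two-sided 5%: 2 × (1.960 + 0.842)² × 72.5/49 = 23.2, so 24 (25 with the t distribution).
- One-sided 5%: 2 × (1.645 + 0.842)² × 72.5/49 = 18.3, so 19 (20 with the t distribution).

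The stated 20 per arm is reproduced only as a one-sided test. At 20 per arm, two-sided power is 72% (noncentral t). The plan's loss assumption leaves 25 × 0.75 = 18.75 per arm; at 18 per arm, two-sided power is 67%.

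**Step 2: effect of baseline adjustment.** With SD s at both times:
- variance of a change score: 2s²(1 − r)
- residual variance after baseline adjustment: s²(1 − r²)
- ratio: (1 + r)/2

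The adjusted SD is 8.51 × √((1 + r)/2). Power is two-sided 5%, noncentral t, with one degree of freedom spent on baseline.

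| r | Variance ratio | Power, 20 per arm | Power, 18 per arm | n per arm for 80% (normal approx.) |
|---|---|---|---|---|
| no baseline term | 1.00 | 72% | 67% | 24 |
| 0.4 | 0.70 | 86% | 82% | 17 |
| 0.5 | 0.75 | 83% | 79% | 18 |
| 0.6 | 0.80 | 81% | 76% | 19 |
| 0.7 | 0.85 | 78% | 74% | 20 |
| 0.8 | 0.90 | 76% | 71% | 21 |

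A second covariate such as gender changes power at 20 per arm by about 0.1 percentage point through the lost degree of freedom.

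**Step 3: chance imbalance.** Under the same assumptions s² = 72.5/(2(1 − r)). A baseline difference of one standard error at 20 per arm, s√(2/20), shifts the change-score estimate by (1 − r) × s√(2/20).
- r = 0.4: s = 7.77; shift = 0.6 × 2.46 = 1.5 mmHg, 21% of 7 mmHg.
- r = 0.8: s = 13.46; shift = 0.2 × 4.26 = 0.9 mmHg, 12% of 7 mmHg.

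**Step 4: unequal variances.** Entry is limited to 135–179 mmHg; week-20 SBP is not. Take, as an illustration, a slope of 0.6 with unit variance at both times before selection, and selection that shrinks baseline variance to 0.64.
- Residual variance: 1 − 0.6² = 0.64.
- Variance of change: 0.64 + (1 − 0.6)² × 0.64 = 0.742.
- Ratio: 0.64/0.742 = 0.86, a 14% reduction.
- Power at 20 per arm: about 78%.

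The observed correlation is then about 0.51. The equal-variance formula would have given a 24% reduction and about 83% power, so it can overstate the gain.

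**The case against.** The strongest reply is that silence is not exclusion. The article lists no model terms of any kind, covariates are commonly left to an analysis plan, and none is shown here. A reader might infer that the plan commits the trial to a raw, unadjusted change score; the text does not say so. A model with change as the outcome and baseline as a covariate gives the same arm effect as one with week-20 SBP as the outcome, so the published sentence is compatible with adjustment. It is also compatible with a mixed model on all SBP values with a common baseline mean, which is about as efficient. Only some implementations lose precision. All of this stands, and it limits the point to an improvement worth stating.

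A reader might also infer that the unadjusted comparison is biased. It is not. Allocation is randomised and both arms pass the same entry threshold, so regression to the mean is expected equally in each. What remains is chance imbalance and lost precision.

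The 72% comes from the sample-size calculation, not from the analysis model; that shortfall is a separate matter. The size of the gain also rests on an unstated correlation and a doubtful equal-variance assumption. Both objections are fair. They change how large the benefit is, not its direction in the cases examined.

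On gender, omitting the stratum errs towards conservative inference, and nothing in the protocol shows that gender predicts SBP change. None of the figures above come from gender.

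**Conclusion.** The point holds as an inexpensive gain in precision. The protocol frames its primary contrast as a change score in both the Sample size and Data analysis sections, and names no baseline or stratum term. If it is fitted that way, the estimate stays unbiased but carries avoidable variance: 10% to 30% under equal variances with r from 0.8 to 0.4, and 14% in the unequal-variance illustration. Adjustment adds roughly 4 to 14 percentage points of two-sided power at 20 per arm and 4 to 15 at 18 per arm.

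It would be wrong to conclude that adjustment rescues the planned power. At 20 per arm it reaches 80% only if r is about 0.6 or lower. At 18 per arm, of the values tabulated, it does so only at r = 0.4. The case for gender is consistency with the stratified design; its gain cannot be computed from the protocol.

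**What to change.** State the primary model in the Data analysis section, for example: SBP (or its change) at weeks 5, 10, 15 and 20, with fixed effects for arm, visit, arm by visit, baseline SBP, baseline SBP by visit and gender, allowing for within-participant correlation. An equivalent is a model of all SBP values with a common baseline mean for the two arms, plus gender. Name the week-20 arm difference in mmHg, with a two-sided 95% CI, as the primary estimate. The secondary outcomes measured at baseline in both arms can take the same form with their own baselines.

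The cost is a sentence or two of text and a few degrees of freedom. No new data are needed. The Trial status section says that recruitment had not begun, so the model can be fixed before any outcome is seen, which also removes a later choice between change-score and adjusted results.
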